#### Key secondary estimand 3 and estimator

5.9.8

A final key secondary estimand is the absolute difference in proportion of SC strategy performed (favourable outcome SC versus unfavourable outcome MAC) between the DIPLANN‐tool in combination with conventional CT imaging and conventional CT imaging alone, in all patients diagnosed with localized kidney cancer who are planned to undergo renal cancer surgery. The same intercurrent events can be expected as for the primary estimand, and these will also be dealt with using the same strategies.

#### Other analyses

5.9.9

Endpoints that are measured repeatedly will be analysed using generalized linear mixed models with a random intercept for patient, including time, arm, a two‐way interaction between time and arm and the stratification factors: whether SC is deemed possible, hospital, and the highest individual PADUA classification in the fixed effects part of the model.

Continuous endpoints measured at one point in time will be analysed using a linear regression model including arm and the stratification factors: whether SC is deemed possible, hospital and the highest individual PADUA classification. Log‐normally distributed endpoints will be log‐transformed before analysis.

Binary endpoints measured at one point in time will be analysed using a binary logistic regression model (with logit link function), including arm and the stratification factors: whether SC is deemed possible, hospital and the highest individual PADUA classification.

#### Missing data

5.9.10

Given the pragmatic design of the study, a few missing data points can be expected. Furthermore, we do not expect that the probability of our endpoint being missing depends on the unobserved value of the endpoint or on the observed values of other recorded values. Therefore, under the assumption of data being missing completely at random (MCAR), a complete‐case analysis will still provide a valid inference.

Endpoints that are measured repeatedly will be analysed using longitudinal likelihood‐based analyses that will make use of all observed data and will provide valid inferences when outcome data is missing at random (MAR).

#### Significance level and confidence intervals

5.9.11

The nominal type I error rate will be controlled at 5%. The hierarchy of endpoint families will be respected. Analysis of secondary endpoints will only be interpreted after demonstration of success on the primary estimand.

The interim analysis for the primary estimand will be performed at the 0.88% significance level and the final analysis at the 4.67% significance level (based on O'Brien Fleming group sequential boundaries).

Bonferroni correction for multiple testing due to multiple key secondary estimands will be applied, setting the significance level at 1.67%.

Subgroup analyses and analyses of other endpoints will be considered as exploratory and hypothesis‐generating.

Any deviation(s) from the original statistical analysis plan will be recorded as a note to file and reported in the final clinical investigation report and publication.

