### Sample size determination

5.3

The study is powered for its primary objective, which targets patients in whom SC is deemed possible either according to the DIPLANN‐tool in combination with conventional CT imaging or according to conventional CT imaging only, as assessed by an independent surgeon between inclusion and randomization.

A sample size of 196 patients in whom SC is deemed possible is needed to achieve at least 80% power to detect an absolute risk difference of 15.6% in favourable outcome (planning and performing as planned a SC strategy) between the DIPLANN‐tool in combination with conventional CT imaging and conventional CT imaging alone, using an exact binomial test at the two‐sided 5% significance level when the design is balanced (1:1 allocation ratio) and the true rate of favourable outcome is 73.4% with conventional CT imaging alone and 89.0% with the DIPLANN‐tool in combination with conventional CT imaging.

The sample size was increased to 198 patients to allow for a 1% drop‐out. The sample size was further increased to 202 patients in whom SC is deemed possible (101 in each group), to foresee an interim analysis for efficacy when 50% of the primary endpoints are measured, using a group sequential design with O'Brien Fleming alpha spending function.

When SC is deemed possible in 86% of patients, the total sample size of patients diagnosed with localized kidney cancer who are planned to undergo renal cancer surgery will be 235. The assumed rate of SC performed as predicted, with a standard of care of 73.4%, is based on other studies.^6^, ^7^

Recruitment will continue until 202 patients in whom SC is deemed possible are randomized.

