#### Key secondary estimand 1 and estimator

5.9.6

One of our key secondary estimands is very similar to the primary estimand, but targets a different patient population, namely all patients diagnosed with localized kidney cancer who are planned to undergo renal cancer surgery (regardless of whether SC is deemed possible). The analysis will be similar to the analysis for the primary estimand, but will include all randomized patients and will be adjusted for whether SC was deemed possible by the independent surgeon (as a main effect).

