#### Key secondary estimand 2 and estimator

5.9.7

Another key secondary estimand is the difference in mean change from baseline (preoperative) in eGFR at 6 months postoperatively, between the DIPLANN‐tool in combination with conventional CT imaging and conventional CT imaging alone, in all patients diagnosed with localized kidney cancer who are planned to undergo renal cancer surgery.

Because eGFR is measured repeatedly (preoperatively, POD1, last measurement before discharge, postoperatively 1 month, 3 months, 6 months, 12 months), we will fit a linear mixed model for eGFR with a random intercept for patient, including time, arm, a two‐way interaction between time and arm and the stratification factors: whether SC is deemed possible, hospital and highest individual PADUA classification in the fixed effects part of the model.

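### Plain Bonferroni at 1.67% for the three key secondary estimands is valid but needlessly conservative; Holm gives the same 5% family-wise control and never rejects fewer hypotheses

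*Protocol article*

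**What the plan says.** Section 5.9.11 of the protocol article fixes the multiplicity rule; it does not leave it open. The overall aim is "The nominal type I error rate will be controlled at 5"%. There is a gate: "Analysis of secondary endpoints will only be interpreted after demonstration of success on the primary estimand". Behind the gate, "Bonferroni correction for multiple testing due to multiple key secondary estimands will be applied, setting the significance level at 1.67"%.

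Sections 5.9.6 to 5.9.8 define three key secondary estimands, all in the full randomized population:

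- Estimand 1: "One of our key secondary estimands is very similar to the primary estimand, but targets a different patient population". It is the primary endpoint analysed in everyone, whether or not selective clamping (SC) was judged possible.
- Estimand 2: "Another key secondary estimand is the difference in mean change from baseline (preoperative) in eGFR at 6 months postoperatively".
- Estimand 3: "A final key secondary estimand is the absolute difference in proportion of SC strategy performed", with main artery clamping as the unfavourable outcome.

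The article states no step-down rule, fixed order or recycling of alpha. It gives no reason for preferring Bonferroni, and no effect size, standard deviation or power for eGFR. Section 5.3 powers the trial for the primary objective only: "A sample size of 196 patients in whom SC is deemed possible is needed to achieve at least 80% power".

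**The concern.** Single-step Bonferroni holds every test at 1.67% whatever happens to the other two. That is wasteful here because two of the three estimands concern the same clamping behaviour as the primary, and they are looked at only after the primary has succeeded. Estimand 1 in particular adds only about 33 patients to the primary analysis set (235 − 202). Given primary success, its rejection is considerably more likely than that of an unrelated endpoint. When it is rejected, Bonferroni returns none of its share of alpha to the tests that remain.

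The third member of the family, eGFR at 6 months, is the only one that measures a patient outcome rather than planning or technique. The Discussion says that earlier studies did not show a clear benefit of SC on renal function, so a modest effect is plausible, and that is where unused alpha matters most.

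**Working it through.** **The plan's own figure.** 0.05/3 = 0.016667, which rounds to 1.67%. The stated level reproduces.

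**Is Bonferroni valid?** Yes. In 400,000 simulated draws under the global null, the family-wise error was 4.9% with independent tests. It was 4.1% when the two clamping statistics correlate at 0.9, so a little alpha goes unused.

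**Why Holm controls the same error.** Order the three p-values and compare them with 5%/3 = 1.67%, 5%/2 = 2.5% and 5%/1 = 5%, stopping at the first non-rejection. If m of the three nulls are true, the first true null to be reached is met no later than step 3 − m + 1. Its threshold is then at most 5%/m, and the Bonferroni inequality over the m true nulls bounds the error by 5% under any dependence. Each Holm threshold is at least 1.67%, so whatever Bonferroni rejects, Holm rejects too.

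**eGFR power at fixed levels.** With z(0.975) = 1.960, z(0.80) = 0.842 and z(0.90) = 1.282:

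- Effect with 80% power at 5%: shift = 1.960 + 0.842 = 2.802. At 1.67%, Φ(2.802 − 2.394) = 0.658. At 2.5%, 0.712.
- Effect with 90% power at 5%: 0.802 at 1.67% and 0.841 at 2.5%.

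With 235 randomized there are about 117 per arm, so 80% power at 5% corresponds to a standardized difference d of about 0.366. At that d, 80% power needs 118 per arm at 5%, 142 at 2.5% and 157 at 1.67%.

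**eGFR power under Holm.** This depends on how often the two clamping estimands are rejected, so it was simulated (200,000 trials per scenario, conditional on primary success at two-sided 5%). Inputs from section 5.3: 73.4% versus 89.0% favourable, 101 per arm with SC possible, which leaves 16 per arm without. Assumptions that are not in the article: no SC in the remaining patients, an eGFR statistic independent of the clamping statistics, and 0%, 30% or 60% of unfavourable cases still ending with SC performed. The clamping tests were run with and without adjustment for whether SC was judged possible.

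Results at d = 0.366 (Bonferroni eGFR power about 0.66 throughout):

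| Unfavourable cases still having SC | Both clamping estimands rejected, adjusted / unadjusted | eGFR power under Holm, adjusted / unadjusted |
|---|---|---|
| 0% | 0.87 / 0.58 | 0.775 / 0.732 |
| 30% | 0.71 / 0.33 | 0.757 / 0.706 |
| 60% | 0.41 / 0.05 | 0.729 / 0.686 |

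Across assumed effects, using power = Φ(d·√(117/2) − z(1−α/2)) for the fixed levels:

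| d | Fixed 1.67% | Fixed 2.5% | Fixed 5% (ceiling) | Holm, range over scenarios |
|---|---|---|---|---|
| 0.25 | 0.315 | 0.371 | 0.481 | 0.346–0.452 |
| 0.366 | 0.657 | 0.712 | 0.799 | 0.686–0.775 |
| 0.5 | 0.924 | 0.943 | 0.969 | 0.935–0.961 |

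The clamping estimands gain too. In the adjusted 30% scenario at d = 0.366, estimand 1 rises from 0.826 to 0.888 and estimand 3 from 0.556 to 0.708. The chance of rejecting at least one of the three is the same under both procedures, because their first steps are identical.

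**The case against.** The strongest reply is that nothing here is wrong. Bonferroni is standard, pre-specified and valid, and the trial was powered only for the primary. That stands: a reader might infer that section 5.9.11 contains an error or fails to control the family, and the document does not support that reading.

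A reader might also infer that both clamping estimands will almost always be rejected once the primary succeeds, so that eGFR is in effect tested at 5%. The article does not support this for estimand 3. Section 3 counts an adjusted or different SC as unfavourable for the primary, whereas section 5.9.8 contrasts SC with main artery clamping, so such cases can count as favourable there. The difference between arms can shrink accordingly. In the simulation, joint rejection of the two clamping estimands fell from 0.87 to 0.41 with adjustment, and to 0.05 without it. Section 5.9.6 specifies adjustment for estimand 1, so the adjusted figures are the fairer guide there, but the uncertainty about estimand 3 is real.

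Nor is eGFR the only test held back: all three are fixed at 1.67%.

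Finally, Holm is not free of cost. Bonferroni has matching 98.33% intervals (100% − 1.67%). A rejection that only Holm makes has p between 1.67% and 5%, where a 98.33% interval will generally include zero. That is a genuine reporting drawback, but a small one. Section 5.9.11 does not give matching intervals as its reason for Bonferroni and states none for the key secondaries.

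**Conclusion.** The point holds as an avoidable inefficiency, not as an error. At the same 5% family-wise level, Holm rejects everything Bonferroni rejects and sometimes more.

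For eGFR, under an assumed effect with 80% power at 5%, power moves from 66% to roughly 69–78%, a gain of about 3 to 12 points. The 14 points from 66% to 80% are a ceiling, reached only if both other estimands are always rejected first. At d = 0.5 the gain is only about 1 to 4 points. These sizes rest on assumed standardized effects, because the article gives no eGFR effect or standard deviation, and on the assumed share of unfavourable cases in which SC was still performed. That Holm never rejects fewer hypotheses rests on no such assumption.

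The 5% statement concerns the key secondary family. Whether the interim and final boundaries of the primary gate are themselves right is a separate question, and it bears on both procedures alike.

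**What to change.** Replace the Bonferroni sentence in section 5.9.11 with Holm's procedure. After primary success, order the three key secondary p-values, compare them in turn with 1.67%, 2.5% and 5%, and stop at the first non-rejection. State that each key secondary is tested once, at its final data cut. If the primary succeeds at the interim, the 6-month eGFR test then still waits for its full data.

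Base significance on Holm-adjusted p-values. If 98.33% intervals are reported, add a note that such an interval may include zero for an estimand rejected only at a later Holm step.

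The cost is one sentence and that note, with no added patients or data. The change should be made before any unblinded results are seen.

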## DISCUSSION

6

In an era where RAPN has emerged as the preferred approach for the treatment of small renal masses, this shift has been accompanied by the progressive integration of advanced technologies aimed at optimizing surgical outcomes. One such innovation is the use of patient‐specific 3D anatomical kidney models. These models have the potential to enhance intraoperative precision by supporting meticulous hilar dissection and improving tumour localization. Additionally, perfusion zone mapping can be superimposed onto the 3D model to delineate vascular territories, thereby guiding selective arterial clamping and contributing to the preservation of uninvolved renal parenchyma.

These models are inherently intuitive and have been shown to improve tumour complexity understanding, facilitate a more selective clamping approach, incur less complications and sometimes even better postoperative kidney function outcomes.^8^, ^9^ As most literature is based on purely retrospective data, we aim to further substantiate these findings in a prospective, randomized, multicentre trial.

In the present trial, renal function was not designated as the primary outcome, as this is influenced by a multitude of factors beyond the mere availability of a 3D model. One such factor could be the adoption of more selective clamping strategies. However, to date, several studies have failed to demonstrate a clear benefit of SC or off‐clamp resection on postoperative renal function.^10^, ^11^, ^12^ It is important to note that many of these studies included patients with preserved baseline renal function, often involved cross‐over from SC to MAC, and did not incorporate the use of 3D models—particularly those incorporating perfusion zone information. Nonetheless, renal function remains a key secondary outcome in this trial and will be analysed in relation to surgical technique, clamping strategy and other perioperative variables. Future research should evaluate the use of 3D models in conjunction with SC in patient populations with impaired renal function (patients with a solitary kidney or chronic kidney disease) or complex renal tumours.

With this RCT, we investigate whether the use of a 3D perfusion zone model increases the successful performance of SC during RAPN. Alongside this, PODRACING includes a comprehensive assessment of patients' health outcomes, patients' insight and surgeons' benefits.
